## Abstract

**Background:**

Long duration spaceflight (i.e., 22 days or longer) has been associated with changes in sensorimotor systems, resulting in difficulties that astronauts experience with posture control, locomotion, and manual control. The microgravity environment is an important causal factor for spaceflight induced sensorimotor changes. Whether spaceflight also affects other central nervous system functions such as cognition is yet largely unknown, but of importance in consideration of the health and performance of crewmembers both in- and post-flight. We are therefore conducting a controlled prospective longitudinal study to investigate the effects of spaceflight on the extent, longevity and neural bases of sensorimotor and cognitive performance changes. Here we present the protocol of our study.

**Methods/design:**

This study includes three groups (astronauts, bed rest subjects, ground-based control subjects) for which each the design is single group with repeated measures. The effects of spaceflight on the brain will be investigated in astronauts who will be assessed at two time points pre-, at three time points during-, and at four time points following a spaceflight mission of six months. To parse out the effect of microgravity from the overall effects of spaceflight, we investigate the effects of seventy days head-down tilted bed rest. Bed rest subjects will be assessed at two time points before-, two time points during-, and three time points post-bed rest. A third group of ground based controls will be measured at four time points to assess reliability of our measures over time. For all participants and at all time points, except in flight, measures of neurocognitive performance, fine motor control, gait, balance, structural MRI (T1, DTI), task fMRI, and functional connectivity MRI will be obtained. In flight, astronauts will complete some of the tasks that they complete pre- and post flight, including tasks measuring spatial working memory, sensorimotor adaptation, and fine motor performance. Potential changes over time and associations between cognition, motor-behavior, and brain structure and function will be analyzed.

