### Objectives

The aim of our studies are to a) identify changes in brain structure and function that occur with spaceflight and prolonged bed rest and characterize their recovery time course; b) assess whether and how these changes impact behavioral and neurocognitive performance; and c) parcel out the contribution of microgravity to the potential brain functional and structural changes.

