### Hypotheses

We hypothesize that measures of brain structure, function, and network integrity will change from pre to post flight in crewmembers, and to a lesser extent in bed rest participants with accumulating time, but not in control subjects. Moreover, we predict that these changes will correlate with indices of cognitive, sensory, and motor function in a neuroanatomically selective fashion.

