#### Testing timeline

Astronauts will be assessed at nine time points: two assessments will take place before launch (approximately 180 days and 90 days before launch), three assessments will take place while in flight (approximately day 30, 90, and 150); and four assessments will take place post flight (approximately 1-4, 30, 90 and 180 days post flight) (see Table 1).

Bed rest subjects will remain in bed with their heads tilted down for 70 consecutive days. Behavioral measures and neuroimaging assessments will be obtained at seven time points: a) two measurements will take place approximately 12 and 7 days before bed rest; b) two measurements will take place at approximately 7 and 30 days in bed rest; and c) three measurements post bed rest: one on 65 days into a 70 day campaign as close to day 0 when the subject gets up from bed (for all measures except those requiring upright stance), day 0 of standing up from bed for tests requiring upright stance, day 8 and 12 after the subject stands up for all tests (see Table 1).

Ground-based control subjects will be completing the exact same measures as the astronauts at four time points, with a one-month interval between each consecutive pair of time points.

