### Image acquisition

Multi-sequence MRI for astronauts and ground-based control subjects will be performed on the same 3 T Siemens Magnetom verio MRI scanner located at UTMB at Victory Lakes. Multi-sequence MRI for bed rest subjects will be performed on a 3-Tesla Siemens Magnetom skyra syngo MRI scanner located at UTMB at Galveston. The scan protocol for astronauts, bed rest subjects and ground-based controls will be identical. For this study we will use a T1-weighted gradient-echo pulse sequence with the following parameters: 3D T1 axial overlay (TR = 1900 ms, TE = 2.44 ms, flip angle = 9°, FOV = 270 × 270 mm, slice thickness = 0.9 mm, 192 slices; matrix = 288 × 288 voxel size = 0.9375 × 0.9375 × 0.9 = 0.7910 mm^3^, duration = ~4 minutes).

For DTI, we will perform a single shot echo planar sequence (TR = 10100 ms, TE = 95 ms, FOV = 240 × 240 mm, slice thickness = 2.0 mm, matrix = 128 × 128, voxel size = 1.88 × 1.88 × 2.0 mm, 75 contiguous slices. Maximum **b**-value was 1000 s/mm^2^ in 30 non-collinear directions, NEX = 2, and two volumes were acquired without diffusion weighting (**b-**value **=** 0 s/mm^2^)) [72]. Acquisition time is ~11 min. All slices are contiguous.

For “Resting State” functional MRI, we will use a single-shot gradient-echo (GRE) echo planar imaging (EPI) sequence [73] to acquire 240 T2*-weighted BOLD images (TR = 3660 ms, TE = 39 ms, flip angle = 90°, FOV = 240 × 240 mm, slice thickness of 4 mm, 1 mm slice gap, matrix = 94 × 94, voxel size = 2.55 × 2.55 × 5.0 mm, 36 axial slices, duration = ~10 minutes). Participants will be instructed to keep their eyes open, to remain awake, look at a fixation point and to not think about anything in particular. A pulse oximeter will be placed on the participant’s finger to record the cardiac signal, both of which will be regressed out prior to data analyses.

For functional MR imaging we will use a gradient echo T2*-weighted echo-planar imaging (EPI) sequence with BOLD contrast (TR = 3660 ms, TE = 39 ms, flip angle = 90°, FOV = 240 × 240 mm, slice thickness of 4 mm, 1 mm slice gap, matrix = 94 × 94, voxel size = 2.55 × 2.55 × 5.0 mm, 36 axial slices). The EPI images will be collected parallel to the AC-PC line.

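### Aim (c), the microgravity contribution, cannot be identified from the end-of-exposure flight versus bed rest contrast, because group is fully confounded with exposure length, recovery state and scanner

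*Protocol article*

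**What the plan says.** The Abstract (Methods/design) states the role of the bed rest group: "To parse out the effect of microgravity from the overall effects of spaceflight, we investigate the effects of seventy days head-down tilted bed rest". The Objectives section states aim (c) as to "parcel out the contribution of microgravity to the potential brain functional and structural changes". The Hypotheses section predicts change in crewmembers and, "to a lesser extent in bed rest participants with accumulating time, but not in control subjects". The Design section announces between-subject as well as within-subject comparisons, and the text after Table 1 says that astronauts and bed rest subjects will be compared on brain structure and function over time.

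The groups differ as follows.

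- **Exposure.** The Abstract describes "four time points following a spaceflight mission of six months". For bed rest, the Testing timeline says: "Bed rest subjects will remain in bed with their heads tilted down for 70 consecutive days".
- **State at measurement.** Astronauts have no MRI in flight and are first assessed about 1-4 days after return. For bed rest, the nearest equivalent is "one on 65 days into a 70 day campaign", except that tests needing upright stance are done on day 0 of standing.
- **Scanner.** Under Image acquisition: "Multi-sequence MRI for astronauts and ground-based control subjects will be performed on the same 3 T Siemens Magnetom verio MRI scanner". Bed rest subjects are scanned on a Skyra at another site.

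The Discussion concedes that the groups are not tested at the same time points and that a group-by-time design would separate microgravity from other factors better, but calls it infeasible. It offers to de-trend astronaut and bed rest data with any drift seen in the ground-based controls. It names neither the unequal exposure nor the two scanners.

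**The concern.** A between-group contrast can speak to the microgravity contribution only if the groups differ in little beyond flight versus tilt. Here, for imaging, every astronaut differs from every bed rest subject in exposure length, recovery state and scanner. No analysis of the end-of-exposure scans can separate these from the factor of interest, because none of them varies within a group.

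Exposure length matters most, because the article's own premises make it plausible. The hypothesis expects change to grow with time, and the Background cites a dose-dependent vascular effect of microgravity. If change is still growing at day 70, bed rest will show less than flight even where tilt reproduces the flight effect completely. That is the predicted pattern, and it would be open to misreading as evidence of spaceflight factors other than microgravity.

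The offered drift correction does not reach bed rest MRI. Controls are scanned only on the Verio and cannot show drift on the Skyra.

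**Working it through.** **1. The article's own figures.** The Sample size section gives a mean change of 1.68 and an SD of 0.60 log sec on the Functional Mobility Test (FMT).

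- Number for a 10% coefficient of variation: (0.60 / 1.68 / 0.10)² = 12.76, rounded up to 13.
- Power with 10 subjects at half the sensitivity (standardised change 0.84 / 0.60 = 1.4; one-sample t-test, two-sided 0.05 assumed): 0.975.

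Both reproduce. Both concern change within one group. The article gives no figure for flight versus bed rest.

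**2. Exposure length alone.** Take six months as 180 days. Suppose tilt reproduces microgravity perfectly and nothing else in flight matters. Under linear build-up the bed rest change is 70/180 = 0.39 of the flight change (65/180 = 0.36 at the day 65 scan). If change levels off exponentially with time constant τ, the ratio is (1 − exp(−70/τ)) / (1 − exp(−180/τ)). The documents give no build-up rate, so τ is assumed and varied:

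| Build-up | Bed rest / flight | Gap due to duration only |
|---|---|---|
| Linear | 0.39 | 61% |
| τ = 180 days | 0.51 | 49% |
| τ = 90 days | 0.625 | 37.5% |
| τ = 60 days | 0.725 | 27.5% |
| τ = 30 days | 0.905 | 9.5% |
| τ = 14 days | 0.993 | under 1% |

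**3. Would such a gap be noticed?** As an illustration, use the FMT mean and SD with 13 per group (normal approximation, two-sided 0.05). The standard error of the difference is 0.60 × √(2/13) = 0.235.

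- Linear: gap 1.68 × (1 − 0.39) = 1.02; 1.02 / 0.235 = 4.4; power about 0.99. At half the sensitivity, power is about 0.59.
- τ = 30 days: gap 1.68 × (1 − 0.905) = 0.16; 0.16 / 0.235 = 0.68; power about 0.10.

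**4. Recovery state.** Let the flight effect decay after return as exp(−d/ρ), with ρ assumed. The Sample size section mentions FMT recovery times of about 15 days; 95% recovery by then would mean ρ = 15 / ln 20 = 5 days. The fraction left at day 1 and day 4 is 0.82 and 0.45 for ρ = 5, and 0.94 and 0.77 for ρ = 15. Dividing the day 65 bed rest ratio, with no recovery, by these fractions gives:

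| Build-up | Bed rest day 65 / flight | Range over ρ = 5 to 15 days and return day 1 to 4 |
|---|---|---|
| Linear | 0.36 | 0.39 to 0.80 |
| τ = 30 days | 0.89 | 0.95 to 1.98 |
| τ = 14 days | 0.99 | 1.06 to 2.20 |

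The true ratio is 1 throughout by construction. The observed ratio can fall well below or well above it. This step applies to measures taken in bed at about day 65, not to the upright tests.

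**5. Scanner.** Each subject stays on one scanner, so a fixed offset cancels in change from own baseline. Scanner-specific drift does not cancel.

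**6. Overlap in Table 1.** Cube rotation, the dual task and sensorimotor adaptation are scheduled on flight day 30 and on bed rest day 30. The next closest pair is flight day 90 and bed rest day 65-70, which are 20 to 25 days apart. No MRI session is matched on exposure.

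**The case against.** A reader might infer that the hypothesis is bound to be confirmed, so that the predicted result, "to a lesser extent in bed rest participants", would appear whatever the truth. The documents do not support that. It needs effects that still grow after day 70, and the Background cites motor changes after missions of up to two weeks and animal changes after 1 to 14 days. With early levelling-off, the duration gap is under 1%. Recovery state works against the prediction, and a fixed scanner offset has no direction in within-subject change. Nor is the bed rest endpoint always taken in bed, since upright tests wait for standing.

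It can also be said that no passage plans a bed rest/flight ratio or a percentage share. Elsewhere the article promises only insight into mechanisms, the Discussion discloses the unmatched time points, and the modelling may be left to an analysis plan that is not shown. Finally, the bed rest sessions at days 7, 30 and 65-70 can show whether change has levelled off.

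All of this stands, and it removes any claim about direction. It does not rescue aim (c). The Abstract and Objectives still promise to separate the microgravity contribution. The disclosed limitation omits exposure length and scanner, and no model can separate factors that coincide with group. The bed rest time course helps with duration only.

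**Conclusion.** The point holds as a problem of identification. The end-of-exposure contrast cannot deliver aim (c), because exposure length, recovery state and scanner each coincide completely with group for imaging. Duration alone could make bed rest look anywhere from under 1% to 61% smaller than flight. The recovery difference shifts the ratio upward, past 1 in some scenarios, so the net bias has unknown size and sign.

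These sizes rest on assumed linear or exponential build-up, assumed exponential recovery with ρ of 5 to 15 days, and six months taken as 180 days. The confounding itself rests only on the stated schedule and scanners. The within-group aims are unaffected. The wording and the aim (c) contrast should be changed.

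**What to change.** - **Tasks also done in flight.** Make within-subject change from own baseline at flight day 30 versus bed rest day 30 the primary aim (c) contrast. Cube rotation in the seated in-flight condition is the cleanest, though bed rest subjects do it lying down. For the dual and adaptation tasks, state that astronauts go from the scanner before flight to a harnessed seated posture in flight, so posture and setting differ. Treat flight day 90 versus bed rest day 65-70 as secondary and approximate.
- **Levelling-off.** Use the bed rest measurements at days 7, 30 and 65-70 to check whether change has levelled off before any comparison with six-month flight.
- **MRI and post-only measures.** Report within-group change. Name exposure length, recovery state and, for MRI, scanner as confounders beside the limitation already in the Discussion. Do not de-trend Skyra data with Verio-only controls. Attribute no share of the change to microgravity, and reword aim (c) to match.

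This changes wording and analysis only and uses sessions already scheduled. The cost is a narrower claim for the imaging outcomes: the matched contrast covers three behavioural tasks and does not by itself answer aim (c) for brain structure and function.

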**Discussion:**

This study explores how spaceflight induced brain changes impact functional performance. This understanding could aid in the design of targeted countermeasures to mitigate the negative effects of long-duration spaceflight.

## Background

Over the last two decades, several studies have been published on the impact of long-duration (i.e., 22 days or longer) spaceflight on the central nervous system (CNS). While the effects of spaceflight on the sensorimotor systems and the resulting difficulties that astronauts experience with posture control, locomotion, and manual control are well documented [1-5], it is unclear if spaceflight is associated with cognitive dysfunction [6]. As a result of poor control conditions and inadequate power in the published studies on the neural correlates of spaceflight, a paucity of knowledge exists. In addition, not much is known about the neural mechanisms underlying the behavioral and potential cognitive changes that occur with spaceflight exposure, or their development and recovery over time. In consideration of the health and performance of crewmembers in flight and post-flight, we are conducting a controlled prospective longitudinal study to investigate the effects of spaceflight on the extent, longevity and neural bases of sensorimotor, cognitive, and neural changes.

### Effects of spaceflight on motor behavior and cognitive functioning

#### Motor behavior

While in space, the visual, vestibular and proprioceptive systems of astronauts adapt to microgravity [5,7,8]. Following their return to earth, astronauts have to readapt to Earth’s gravity. During this re-adaptation period disturbances have been reported in spatial orientation, posture, gait, and eye-hand coordination [5,9], which can potentially be ascribed to the central reinterpretation of multiple sensory inputs [8].

Studies conducted at National Aeronautics and Space Administration (NASA) Johnson Space Center’s Neuroscience Laboratories on the effects of spaceflight on human motor behavior have reported post-flight changes in locomotor control and body segmental coordination. Studies including subjects that completed missions with a duration of up to two weeks showed alterations in muscle activation variability [10], increased variability in ankle and knee joint motion [11], alterations in head-trunk coordination and reduced visual acuity during walking [12], impairment in the ability to coordinate effective landing strategies during jump tasks [13], with poorer balance and problems with postural stability lasting up to ten days post-flight [5,8,14,15]. In addition to alterations in muscle activation variability [16-18] that were observed after short duration missions, disruptions in lower limb kinematics leading to reduced toe clearance [19], and poorer ability to complete challenging locomotor maneuvers [20] were observed in subjects after long-duration spaceflight missions (i.e. with a duration of three to six months).

Most of the post-flight vestibulo-motor disturbances have been attributed to reorganization of information from the otoliths specifically, which signal orientation of the head with respect to a gravitational reference vector [21]. However, it is clear that behaviors mediated by intravestibular interaction of the semicircular canals and otoliths are affected by microgravity exposure as well [22]. Other proposed mechanisms for the association between microgravity and reduced motor control abilities include changes in bodily fluid shifts that result in disruption of thalamic function [23], and direct effects on the ocular and visual neural systems [24]. Moreover there may be neuroplasticity occurring in association with adaptive behavioral modifications as astronauts learn to control their movements in the microgravity environment. These adaptations may be the result of restitution and/or substitution of control processes. Restitution refers to functional recovery through physiological recovery as a result of spontaneous tissue heal and neural pathway re-activation. Substitution is the functional restoration via system reorganization, where certain brain areas are recruited to take over the function of previously relied upon brain regions, or compensation which refers to adaptation on the functional and neural levels [25]. Which of these principles are responsible or play the bigger role in astronaut’s adaptation to the microgravity environment is yet to be discovered.

#### Cognition

Although studies have reported little to no change in overt cognitive abilities during flight and post-flight while using available monitoring technology, the few studies that have investigated the effects of spaceflight on cognition in humans reported that dual-tasking of cognitive and motor behaviors is significantly impaired during the initial period of adaptation to a microgravity environment [26-28] and over a longer six month mission [2]. Furthermore, they indicated that the increased demands of motor control in space can interfere with simultaneous cognitive task performance. However, results from a recently published review emphasized that due to inadequate study designs it remains unclear whether and how spaceflight is associated with cognitive dysfunction [6].

### Central nervous system plasticity

Whether and to what extent the reported sensorimotor and potential cognitive changes are related to spaceflight-induced brain structural changes, apart from vestibular reorganization, or more peripheral changes such as muscle unloading and bodily fluid shifts, is not yet known. However, existing evidence supports that the brain may undergo structural and functional remodeling similar to that seen in bone and muscle, as a result of the interaction between exposure to microgravity, vascular changes, and radiation associated with spaceflight. Plasticity may occur, including cortical reorganization associated with sensorimotor adaptation, compensatory processing, and brain volumetric alterations [14,29-32].

#### Microgravity

To the best of our knowledge, no studies have examined the potential effects of microgravity on brain structure in humans. However, animal research demonstrates structural brain changes after microgravity exposure. These effects were most notable in the somatosensory cortex [29,30,33,34] and the cerebellum [29] and include a decreased number of synapses and the degeneration of axonal terminals. Ross (1993, 1994) has demonstrated that hair cells in the rat utricular macula, the part of the vestibular system that perceives changes in longitudinal acceleration and gravity, undergoes extensive plasticity as a result of spaceflight, with a 40% to 55% increase in synapse number [31,32]. This plasticity remained evident following flight, even after posture control in the rats had returned to normal, suggestive of compensatory post flight control processes. Moreover, these results were observed in animals after one [29], nine [31,32], and fourteen days [33] in a microgravity environment.

#### Indirect effects of microgravity: vascular changes

Changes in cerebral blood flow as a result of microgravity exposure may also contribute to brain reorganization. Following spaceflight, astronauts have reduced arterial pressure and cerebral blood flow velocity as measured with transcranial Doppler (i.e. ultrasound) [35]. Similarly, Gazenko et al. [36] found that astronauts show reduced cerebral blood flow pulsatility, as measured with impedance rheography (a method used to study the filling of a part of the body with blood by graphically recording the fluctuations in the resistance of that part of the body), when in a head-down tilt posture following spaceflight. Other studies have demonstrated a microgravity dose-dependent effect, with cerebral vasoconstriction following long-term flight not resolved after a period of five weeks [36,37]. It is hypothesized that this increased vasoconstriction is an adaptive response to the increased cranial pressure experienced while in the microgravity environment. Blood vessel remodeling can occur relatively quickly, with as little as two weeks of head-down tilt on Earth resulting in increased vessel wall thickness and vessel diameter in the brain vasculature and concomitant decreases in the lower extremity vasculature [38,39].

